**Fig 1 pone.0300250.g001:**
[figure not shown]
The schedule of enrolment, interventions, and assessments *. *Recommended content can be displayed using various schematic formats. See SPIRIT 2013 Explanation and Elaboration for examples from protocols. **List specific timepoints in this row.

Patients will be included in the study if they: (a) are 18 years or older; (b) have a documented diagnosis of coronary heart disease including acute myocardial infarction (AMI) (Non ST and ST elevation MI), patients with unstable angina, and patients with stable angina; (c) have access to a computer, and (d) agree to participate.

The exclusion criteria include: patients who are (1) with a history of psychiatric and neurological disorders; (2) unable to speak or understand Arabic; (3) with impaired bilateral hearing, or visual impairment which limits the use of computers; (4) with contraindications or severe physical disabilities that limit patients from participation; Additional exclusion criteria will be applied if patients are not able to understand the procedure and the aims of the study after full explanation.

By using the results of a meta-analysis published in 2017 [5] for an incidence of a major cardiovascular event of 13.8% in the intervention group and 38.6% in the control group, with a power of 80% and a first-species risk α of 0.05, we found a size of 56 patients in each group.

All investigators in this study will attend rigorous training on data collection and research protocol.

Training sessions will be thorough, and detailed. The purpose of this rigorous training is to ensure that all investigators have a comprehensive understanding of the data collection methods and research protocols relevant to the study.

The research protocol encompasses the set of guidelines, procedures, and ethical standards that govern how the research study will be conducted. It includes considerations such as participant recruitment, informed consent, data handling, confidentiality, and data analysis methods.

These sessions will be held before the start of the survey to prevent measurement bias. In addition, all investigators are trained in the principles of therapeutic education.

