### Intervention group

Patients assigned to the intervention group will first receive therapeutic education. The digital platform will then enable care providers to support them remotely.

A questionnaire will be distributed to patients before they begin the TPE program, in order to assess their knowledge of the disease, their eating habits, their physical activity, etc.

The same questionnaire will be distributed again at the end of the intervention, to study the impact of the TPE program in terms of knowledge retention.

Participants assigned to the intervention group will be divided into sub-groups. Each group will receive three TPE sessions. Educational sessions will be held once every week.

TPE sessions will include theoretical presentations on the pathophysiology of coronary artery disease, its risk factors, therapeutic objectives and therapeutic management.

These sessions will also include practical workshops using video sequences, role-playing and card games, covering heart attack alert, biological and blood pressure therapeutic objectives, the Mediterranean diet, the different commercial presentations of drugs, and types of social coverage.

At the end of each session, a round-table discussion will be held on the daily life of a coronary sufferer: physical activity/stress management/smoking/returning to work.

During the last session, each patient will benefit from an individual interview during which a lipid and glycemic assessment will be requested to evaluate the impact of the TPE in the medium term.

In addition, each patient will receive leaflets in Arabic, summarizing what will be presented during the TPE sessions.

At 3 months after completion of the TPE program, the same questionnaire will be redistributed, a biological check-up will be requested, and a quality-of-life assessment will be carried out.

In a second phase, the intervention group will be monitored via a digital platform.

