### Outcomes

#### Primary outcome

The primary outcome of this study is the occurrence of major cardiovascular events in the year following hospital discharge for the control group, and in the year following completion of the TPE program with digital follow-up for the intervention group.

The primary outcome is based on the occurrence of acute myocardial infarction, stable angina, coronary revascularization, stroke, hospitalized heart failure, or death attributable to any cardiovascular disease [15]. Information on the primary outcome will be systematically obtained through follow-up interview at 12 months and confirmed by reviewing patients’ medical records. If a patient dies during follow-up, this information will be obtained directly from patient’s family or confirmed by physician.

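### The primary composite counts coronary revascularization without excluding procedures already planned at randomisation, which dilutes the effect or, given the unequal follow-up windows, can favour the intervention

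*Protocol article*

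**What the plan says.** All references are to the protocol article.

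- **Primary outcome** lists the components as "acute myocardial infarction, stable angina, coronary revascularization, stroke, hospitalized heart failure, or death attributable to any cardiovascular disease", citing a reference. Heart failure must be hospitalized and death must be cardiovascular, but revascularization has no qualifier.
- **Settings and participants** (eligibility) admits patients with "coronary heart disease including acute myocardial infarction (AMI) (Non ST and ST elevation MI), patients with unstable angina, and patients with stable angina". The Intervention section places the baseline blood pressure, glucose and lipid measurements during the hospital stay.
- **Primary outcome** counts control events "in the year following hospital discharge for the control group". The other arm's clock starts at a later point: its events are those "in the year following completion of the TPE program with digital follow-up for the intervention group". Under Intervention group: "Each group will receive three TPE sessions. Educational sessions will be held once every week".
- **Primary outcome**, ascertainment: information is "systematically obtained through follow-up interview at 12 months and confirmed by reviewing" the medical records. No step sorts procedures into planned and unplanned.
- **Settings and participants** (sample size) uses a meta-analysis "for an incidence of a major cardiovascular event of 13.8% in the intervention group and 38.6% in the control group", with 80% power and α of 0.05, giving 56 patients per group.

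**The concern.** A patient admitted with coronary disease may leave hospital with a further coronary procedure already scheduled. That procedure treats the disease that made the patient eligible. It was decided before allocation, and neither the education sessions nor the platform can prevent it. Under the stated definition it still scores a primary event, and the record review would confirm it because it did take place.

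Two things are at stake. Events that the intervention cannot influence weaken the contrast between the arms if they occur equally in both. And because the two arms start their clocks at different points, procedures done soon after discharge may be counted in one arm and not in the other, which is bias rather than noise.

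**Working it through.** **Inputs from the document.** p_I = 0.138 (intervention), p_C = 0.386 (control), n = 56 per arm, α = 0.05, power 80%. Sidedness is not stated; two-sided is used because it reproduces the plan's figure.

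**Step 1: reproduce the plan's sample size.** Pooled rate (0.138 + 0.386)/2 = 0.262; difference d = 0.248.

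n = [1.960·√(2·0.262·0.738) + 0.842·√(0.138·0.862 + 0.386·0.614)]² / 0.248² = 48.2, rounded up to 49.

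With continuity correction: (n/4)·[1 + √(1 + 4/(n·d))]² with n = 48.15 gives 55.9, so **56 per arm**, an exact match. The sample-size arithmetic is not at fault. Power at 56 per arm is 85.7% by the uncorrected normal approximation and 81.5% by Fisher's exact test.

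**Step 2: dilution, if planned procedures fall equally in both arms.** Assumption: a share s of each arm has a planned procedure inside the window, independent of other events and on top of the design rates. The document gives no value for s, so 5% to 20% is shown (about 3 to 11 patients per arm).

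Observed rate = 1 − (1 − p)(1 − s). Example at s = 5%: control 1 − 0.614·0.95 = 0.417; intervention 1 − 0.862·0.95 = 0.181.

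| s | Control | Intervention | Difference (points) | Risk ratio | Power, normal | Power, Fisher |
|---|---|---|---|---|---|---|
| 0 | 38.6% | 13.8% | 24.8 | 0.36 | 85.7% | 81.5% |
| 5% | 41.7% | 18.1% | 23.6 | 0.43 | 78.5% | 73.2% |
| 10% | 44.7% | 22.4% | 22.3 | 0.50 | 71.1% | 65.2% |
| 20% | 50.9% | 31.0% | 19.8 | 0.61 | 57.1% | 49.0% |

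**Step 3: bias, if planned procedures fall in the gap.** The control window opens at discharge; the intervention window opens after three weekly sessions. Take the extreme case: no true effect, and every planned procedure done after discharge but before the programme ends. Then the control rate is p + s(1 − p) and the intervention rate stays at p. The chance of a significant result favouring the intervention, nominally 2.5%, becomes:

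| Base rate p in both arms | s = 5% | s = 10% |
|---|---|---|
| 13.8% | 9% | 22% |
| 38.6% | 5% | 10% |

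This is an upper bound for these values of s, since some planned procedures would fall later and count in both arms. With half of them in the gap, the figures are 5% and 8% at the lower base rate, and 4% and 5% at the higher.

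**Step 4: how many events would change the result.** At the design rates, 56 × 0.386 ≈ 22 control events and 56 × 0.138 ≈ 8 intervention events. Adding events to the intervention arm alone, Fisher's test loses significance at 22 vs 12 (p = 0.064) and Pearson's chi-square at 22 vs 13 (p = 0.067). That is a net shift of 4 to 5 events in one direction.

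**The case against.** **This is detail that an article leaves elsewhere.** The composite is one sentence with a citation, and the cited source or a full protocol may define revascularization more narrowly. That is possible and keeps confidence at moderate. But the article states the components as the rule, qualifies two of them and not this one, and nothing elsewhere narrows it. Applied as written, it counts the wrong procedures.

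**The documents do not show that planned procedures occur.** Correct: eligibility gives diagnoses only, and no share of scheduled procedures appears. The diagnoses make them plausible; their frequency is unknown.

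**The power loss may be overstated.** This stands. The 38.6% and 13.8% come from a meta-analysis that is not shown. If those rates already include planned procedures, the loss shrinks or vanishes. Stable angina is also a component, so a patient awaiting a procedure may already be counted, and the independence assumed in Step 2 would then exaggerate the added events.

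**Stronger readings that the documents do not support.** A reader might infer that the only effect is dilution towards a risk ratio of 1. The different window starts rule that out, since early procedures can count in control only. A reader might also infer that a chance imbalance of a few scheduled procedures would decide the trial. At the plan's own rates it takes a net shift of 4 to 5 events, while the 5% scenario yields only about 3 planned procedures per arm in total.

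**Conclusion.** The point holds as a defect in the endpoint definition. The component admits procedures fixed before randomisation, in a population where they are plausible and with a control window that opens at discharge.

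The direction depends on timing: dilution when the procedures fall in both windows, bias in favour of the intervention when they fall between discharge and the end of the education programme. The documents do not show which would dominate.

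The size cannot be derived from the documents. The fall in power from about 86% to between 79% and 57% illustrates assumed shares of 5% to 20% added independently to the design rates. It does not show that the trial is underpowered. Even if the power loss were nil, the primary outcome would still include events that the intervention cannot prevent. Confidence is moderate.

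**What to change.** 1. In Primary outcome, define the component as *coronary revascularization not already planned at the time of randomisation*.
2. On the baseline form, before allocation and in both arms, record any coronary procedure already scheduled. At the 12-month record review, classify each procedure against that form, so that the decision rests on a pre-allocation record and not on a judgement made once the group is known.
3. Report the composite with all revascularizations as a sensitivity analysis.

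This closes the route by which planned procedures feed the unequal windows. It does not align the windows themselves, which is a separate matter.

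**Cost.** One phrase and one line on a form. Fewer events are counted: in the 20% scenario about 7 fewer in control (56 × 12.3 points) and 10 fewer in intervention (56 × 17.2 points). The restricted definition may also differ from the one behind the 38.6% and 13.8%, so the sample-size source should be checked for how it counted revascularization. The change concerns endpoint counting only and leaves clinical care untouched.

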At the end of the TPE program, the medical team verifies eligibility for the digital platform program. A "therapeutic support" contract is signed by the program participant and the medical team, setting out the therapeutic objectives during follow-up, as well as the parameters to be collected and transmitted to the platform.

The TPE team will educate the patient in the use of the mobile application, which is based on the codes and uses of consumer applications.

*Second step: digital monitoring phase*

Every day, the patient will be invited to transmit the monitoring parameters set out in the "therapeutic support" contract.

Data will be transmitted asynchronously and securely on the monitoring platform.

*Third step: Data analysis phase*

The medical team can interact with the patient via the platform. If necessary, the patient can be called into the center by the medical team for reassessment and early consultation, in order to optimize his or her care pathway.

*Forth step: Assessment phase*

At 12 months, an assessment of knowledge retention will be carried out, as well as the incidence of major cardiovascular events.

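### Primary events enter the count only through a 12-month patient interview, while only the intervention arm is monitored daily, so the chance of detecting contact-dependent events can differ by arm

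*Protocol article*

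**What the plan says.** The protocol article, under Primary outcome, defines the composite as "acute myocardial infarction, stable angina, coronary revascularization, stroke, hospitalized heart failure, or death attributable to any cardiovascular disease". Information on it "will be systematically obtained through follow-up interview at 12 months and confirmed by reviewing" the patients' medical records. For deaths: "If a patient dies during follow-up, this information will be obtained directly from" the patient's "family or confirmed by physician". The interview and record check are described once, with no distinction by arm.

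Contact during follow-up does differ by arm. In the section on the therapeutic digital platform, intervention patients sign a support contract, and then: "Every day, the patient will be invited to transmit the monitoring parameters set out in the" contract. The dashboard has an alert module, there is a messaging channel, and "If necessary, the patient can be called into the center by the medical team for reassessment and early consultation". Under Control group, controls have the usual hospital controls, with neither the education programme nor digital monitoring.

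**The concern.** Two features combine. First, the interview is the source and the records are the check. An event that a patient forgets, misnames or does not mention is not looked for under the rule as written. Second, the arms differ in how often anyone has occasion to notice a symptom, write it down and make it memorable to the patient, who is the interview respondent and knows the allocation.

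The composite is exposed to this to differing degrees. Stable angina depends most on contact with care and on judgement. It is also one of the entry diagnoses under Settings and participants, so calling it a new event needs a decision. Myocardial infarction, stroke and cardiovascular death are less open to it. The death component depends on cause, yet the stated rule can be met by the family's account alone.

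At stake is the primary comparison. Unequal detection could hide a real benefit or produce an apparent one, and a larger sample would not correct it.

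**Working it through.** **Inputs.** From Settings and participants: 13.8% intervention, 38.6% control, power 80%, α 0.05, 56 per group. From Data analyses: Pearson chi-squared or Fisher's exact test for percentages. Sidedness is not stated; two-sided is assumed. The article gives no detection rates, so every detection figure below is an assumption.

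**Step 1: the plan's own figure.** Mean rate (0.138 + 0.386)/2 = 0.262; difference 0.248.

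- Uncorrected: n = [1.960·√(2·0.262·0.738) + 0.842·√(0.138·0.862 + 0.386·0.614)]² / 0.248² = (1.219 + 0.502)² / 0.0615 = 48.2, so 49.
- Continuity-corrected: (48.15/4)·[1 + √(1 + 4/(48.15·0.248))]² = 55.9, so 56.

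The stated 56 reproduces. The sample-size figure is not at issue here.

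**Step 2: method for the rest.** Enumerate all pairs of event counts at 56 per arm under two binomial distributions. Sum the probabilities of the pairs for which the uncorrected Pearson chi-squared test is significant at two-sided 0.05. With equal and complete detection at 13.8% v 38.6%, power is 86.6%.

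**Step 3: true effect as planned, unequal detection.**

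| Assumption | Recorded rates, intervention v control | Power |
|---|---|---|
| Equal, complete detection | 13.8% v 38.6% | 86.6% |
| 3 extra points in intervention arm (56 × 0.03 = 1.7 patients) | 16.8% v 38.6% | 74.6% |
| 5 extra points (2.8 patients) | 18.8% v 38.6% | 65.0% |
| 8 extra points (4.5 patients) | 21.8% v 38.6% | 49.9% |
| Only controls under-detected, 90% found | 13.8% v 34.7% | 75.2% |
| Only controls under-detected, 80% found | 13.8% v 30.9% | 59.8% |
| Both arms 80% found | 11.0% v 30.9% | 75.7% |
| Only intervention arm under-detected, 80% found | 11.0% v 38.6% | 94.1% |

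The last row runs the other way: if engaged intervention patients under-report, the apparent benefit is inflated.

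**Step 4: no true effect, 38.6% in both arms.**

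| Detection in one arm (other arm complete) | False-positive rate |
|---|---|
| 100% | 4.8% |
| 95% | 5.4% |
| 90% | 7.0% |
| 80% | 13.9% |
| 70% | 26.1% |

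At 80%, 13.7 of the 13.9 points favour whichever arm is under-detected. At a true rate of 26.2% in both arms, the same 20% shortfall moves the rate from 5.0% to 10.1%.

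**The case against.** The strongest reply is that the written rule is already common to both arms: one interview at 12 months with a record check. Platform data are not named as an event source. All participants have three data-collection points and controls keep their usual hospital visits. This stands. A reader might infer that the ascertainment rule itself differs by arm, and the text does not support that. What differs is the opportunity for detection.

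A reader might also infer that whoever classifies events knows the allocation. The article does not say who interviews or classifies, or whether they are masked, and a condensed article may leave that to the full protocol. The statement that "all investigators are trained in the principles of therapeutic education" does not settle it. Only the patients' knowledge of their arm follows from the design.

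Call-in is conditional, not routine. Early consultation is also part of the tested intervention, so a revascularisation or heart-failure admission that follows it may be a real consequence and not an artefact. The detection argument is therefore strongest for stable angina.

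The wording on deaths may refer only to learning that a death occurred, with the record check in the preceding sentence still applying. That reading is possible, but the wording does not secure it.

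Finally, if events are missed equally in both arms, less is lost: 75.7% power with 20% missed in both arms, against 59.8% if only controls miss them. This also stands. The harm beyond ordinary loss of events depends on a difference between arms, whose size the documents do not give.

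**Conclusion.** The point holds in a limited form. As written, events that patients do not report have no route into the primary count, and arm-dependent contact means that contact-dependent components can be detected unequally under a nominally common rule. Cause of death can rest on family report alone.

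The size is illustrative. It rests on assumed detection gaps, 56 per arm, the planned rates and a two-sided uncorrected chi-squared test. A few recorded events matter: about two to five extra intervention patients take power from 87% to between 75% and 50%. A 20% shortfall in one arm nearly triples the false-positive rate under no effect, from about 5% to 14%. The direction is not known, so it would be wrong to read the power losses as the expected result. The finding does not rest on any claim about assessor masking.

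The article also starts the 12 months differently by arm: "in the year following hospital discharge for the control group, and in the year following completion of the TPE program" with digital follow-up. That is a separate matter, but it bears on any record search, which needs one definition of the window.

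**What to change.** 1. Review the hospital records of all 112 patients, whatever the interview reports, over a 12-month window defined the same way in both arms.
2. If the full protocol does not already provide for it, have a cardiologist already on the team classify each event from an extract with arm and platform data removed.
3. Require a record or a physician's confirmation before a death counts as cardiovascular; family report may still signal that a death occurred.
4. Report cardiovascular death, myocardial infarction and stroke as a supportive endpoint less open to differences in detection.

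The cost is extra chart abstraction and redaction by existing staff, plus one more table. Treatment, sample size and visits are unchanged. The limit should be stated in the plan: the site's records may still be fuller for intervention patients, and control events treated elsewhere may be missed, so the bias is reduced but not removed.

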#### Secondary outcomes

The secondary outcomes of the study include changes in health behaviors (smoking cessation, adoption of a healthy diet, physical activity), medication adherence, cardiovascular health score and health-related quality of life which will be assessed using the validated Tunisian version of the SF-12 health survey [16].

### Variable definitions

The American Heart Association defines the ideal cardiovascular health as simultaneous presence of four ideal health behaviors and three ideal metabolic indicators [17]. The four ideal health behaviors include nonsmoking, body mass index (BMI) < 25 kg/m2, physical activity at targeted level, and dietary consumption being consistent with current recommended guidelines. The three ideal metabolic indicators are identified as clinical parameters for blood pressure < 120/80 mm Hg, total cholesterol < 5.17 mmol/L (200 mg/dL) and fasting glucose < 5.60 mmol/L (100 mg/dL). Each component of the cardiovascular health metrics will be dichotomized as 1 (ideal status) or 0 (intermediate or poor status).

The validated Tunisian version of the SF-12 health survey (16) produces two summary scores: the Physical Component Summary (PCS) and the Mental Component Summary (MCS). These scores are standardized to have a mean of 50 in the general population, with a standard deviation of 10. Higher scores indicate better health-related quality of life.

